The most frequently encountered pathological entity in TBI patients is an acute intracranial hematoma. Specifically, an acute subdural hematoma (ASDH) is the most common injury in elderly TBI patients and is often accompanied by a cerebral contusion [8, 9]. The enlarged subdural space of the progressively atrophic aging brain is associated with increased tension on bridging veins, making them more susceptible to shearing damage. Furthermore, the widespread use of anticoagulants and antiplatelet drugs among elderly increases the risk for ASDH development, even after low to moderate energetic head trauma [10]. Traditionally, older age has been closely associated to poor outcome after TBI [11, 12], partly because of comorbid illnesses negatively influencing outcome [12]. In reports from the 1980s and 1990s, mortality rates for patients aged ≥65 with an ASDH approached 90% [13, 14]. Hence, elderly patients have long been treated less “aggressively” compared to the younger patient population because of the presumed poor prognosis [10]. Over time, with faster transfers directly from accident to level I trauma hospitals, improved diagnostic tools and acute medical and intensive care, mortality rates in elderly patients with ASDH have declined from 90 to between 30 and 60% [15]. Along with this, neurologists’, trauma- and neurosurgeons’ traditional reserved attitude towards elderly patients has gradually shifted towards a more “aggressive” surgical approach [16, 17]. Despite this trend towards a more intensive treatment approach in the elderly sustaining TBI, the question whether to surgically or conservatively manage elderly patients with an ASDH remains a matter of huge controversy [18]. Surgical evacuation of the hematoma can be lifesaving, but is not necessarily restorative and may leave patients in a questionable quality of life, with huge costs to family and society [19–22]. Conversely, non-operative management may prompt favorable outcome in some patients, but can also result in—potentially preventable—death and disability [23, 24]. At present, it is not possible to accurately predict whether a specific patient will benefit from a certain treatment in terms of survival, functional recovery, and quality of life. This heterogeneity can be caused by many factors, including gender, anticoagulant/antiplatelet use, premorbid functioning, comorbidities, age, and the presence or absence of intracerebral contusions accompanying the ASDH. Current Brain Trauma Foundation (BTF) guidelines for the surgical management of TBI recommend the surgical removal of an ASDH measuring > 10 mm or when it causes a midline shift > 5 mm, regardless of a patient’s neurological state (Glasgow Coma Scale (GCS) score) [25]. These guidelines, released in 2006, are based on low-grade (class C) evidence from the 1990s and thus provide only limited guidance in modern clinical practice, allowing for subjective care and practice variation [23–26]. Indeed, great variation in BTF guideline adherence has been reported, ranging from 18 to 100% between studies [27, 28]. Moreover, major practice variation exists in Belgium and The Netherlands with regard to the management of traumatic ASDHs between centers, and even between neurosurgeons in the same center [29–31]. This variability in TBI management goes alongside unexplained variability in outcome and large between-center differences unrelated to case-mix [32–34].

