#### Exclusion criteria

A potential subject who meets any of the following criteria will be excluded from participation in this study:
Additional epidural hematoma (EDH) or infratentorial (e.g., cerebellar) intracerebral hemorrhage (ICH)Major traumatic abdominal or thoracic injury (each separately defined as an Abbreviated Injury Scale (AIS) score ≥ 4) [66, 67] or a “moribund” state at presentation (e.g., bilaterally absent pupillary responses)Known terminal condition resulting in a life expectancy of less than 1 yearSevere and progressive dementia or cerebral infarction necessitating daily care in a nursery home in the pre-trauma period

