#### Other study parameters

With regard to the second research question, the investigators aim to identify subgroups of patients who will benefit substantially from one of the proposed treatments. It should be noted that these subgroup analyses are explorative in nature as this trial has been powered based on the primary effect estimate.

The following subgroups will be investigated:
Elderly with accompanying cerebral contusions visible on first CT versus isolated ASDHs“Younger elderly” (aged 65–80 years) versus “older elderly” octogenarians (aged > 80 years)Elderly receiving specific oral anticoagulants or antiplatelets versus elderly not receiving such medication*Pre-trauma premorbid functionally independent of minimally dependent elderly (FIM score 4–7) versus functionally dependent elderly (FIM score 1–3) [69, 81]Elderly with severe comorbidities (ASA III-V) versus elderly with mild or no comorbidities (ASA I/II) [82, 83]Male versus femaleSurgical technique: basic hematoma removal by craniotomy versus add-on decompressionNo ICP monitoring versus ICP guided treatment taking into account cerebral perfusion pressureSubgroups stratified on (automatically generated) measurements of volumes and ratio of volumes of important intracranial traumatic findings on non-contrast CT in the acute phase

*A subdivision will be made between anticoagulants (e.g., coumarin derivatives/heparin/DOACs) and antiplatelets (e.g., aspirin/clopidogrel/dipyridamole).

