### Sample size {14}

The sample size of 300 patients was based on an ordinal analysis method of the primary outcome. It was calculated analytically using PASS software version 11 and achieves a 90% power to detect a change in the log odds ratio of 0.69 with a 0.05 (two-sided) significance level, allowing for a loss of follow-up of 8%. Calculations were based on the expected percentage distribution of conservatively treated patients over the GOS-E categories 1–8 (15, 10, 10, 10, 10, 10, 15, 20) with category 1 and 2 combined and an estimated (adjusted) proportional odds ratio of 2.0 representing the targeted treatment effect that is considered clinically relevant in the management of elderly with a traumatic ASDH. Table 4 shows the corresponding distribution of patients over the GOS-E outcome categories. The rationale for combining GOS-E categories 1 and 2 in the statistical analysis is the opinion of the researchers that a potentially large shift of patients from category 1 (death) to category 2 (vegetative state) should not result in a positive trial as this cannot be considered a beneficial or positive effect of surgery.

**Table 4 Tab4:** Estimated shift over GOS-E outcome categories

GOS-E	1&2	3	4	5	6	7	8
Patient’s condition	Dead and vegetative state	Lower severe disability	Upper severe disability	Lower moderate disability	Upper moderate disability	Lower good recovery	Upper good recovery
Initial conservative treatment (%)	25	10	10	10	10	15	20
Early surgery (%)	14	7	8	9	10	19	33

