## Assignment of interventions: allocation

### Sequence generation {16a}

Randomization will take place with a 1:1 allocation ratio via a web-based randomization program by the treating clinician or including researcher and will be stratified by center and blocked with alternating block sizes of 2, 4, and 6. The randomization process will be recorded by the web-based randomization system. A 24-h randomization service will be backed by 24-h availability of the research team, who will also be able to advise on patient eligibility. In case of web-related problems, the treating clinician or including researcher will undertake randomization instead by manually opening a prefabricated sealed envelope containing a category.

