## Statistical methods

### Statistical methods for primary and secondary outcomes {20a}

The primary outcome in this study will be the GOS-E at 1 year. Traditionally, such outcome scales are analyzed by dichotomizing the ordinal scale into a binary scale by defining outcome as “unfavorable” or “favorable” and calculating an odds ratio. However, many patients will not have a realistic opportunity to cross the threshold between “unfavorable” and “favorable” and will therefore not contribute data to the analysis. The crude odds ratio is thus not a meaningful effect measure for a large number of patients and discards much relevant information, reducing both the clinical relevance of the results and the statistical efficiency of the analysis. Therefore, the researchers consider it more appropriate to quantify effects across the full range of the GOS-E. In line with the IMPACT recommendations (NIH-funded International Mission for Prognosis and Analysis of Clinical Trials in TBI project), the investigators plan to analyze the primary outcome by using a proportional odds regression with covariate adjustment for age, GCS, and pupillary reactivity to adjust for baseline imbalances and to optimize statistical efficiency. Ordinal methods have been shown to increase statistical power substantially compared to traditional dichotomous analyses, equivalent to allowing a reduction of over 40% in the sample size without loss of statistical power. The primary effect estimate will be the adjusted proportional odds ratio with 95% confidence interval for the shift in the direction of a better outcome on the GOS-E. Ordinal logistic regression analysis is similar to logistic regression analysis, except for the fact that it estimates multiple odds ratios instead of one. The number of odds ratios is equivalent to the number of categories minus one. The final estimated effect size is a pooled estimate of the common odds ratio. The ordinal regression model assumes that the odds ratio for each potential cut of the GOS-E is constant no matter which cut-off point is taken (proportional odds assumption). Although the common odds ratio is formally only valid if the proportional odds assumption is met, the common odds ratio can be interpreted as a summary measure of treatment effect, even if the odds ratios differ by cut-off [89, 90].

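### The primary proportional-odds model omits centre, the only stratification factor; a random centre intercept would make the analysis match the randomisation at no data cost

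*Protocol article*

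**What the plan says.** Protocol article, Sequence generation {16a}: "Randomization will take place with a 1:1 allocation ratio", and allocation "will be stratified by center and blocked with alternating block sizes of 2, 4, and 6". No other stratification factor is named.

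Protocol article, Statistical methods for primary and secondary outcomes {20a}: the primary outcome is to be analysed by "proportional odds regression with covariate adjustment for age, GCS, and pupillary reactivity to adjust for baseline imbalances". The same section gives statistical efficiency as a second purpose of the adjustment and makes the adjusted common odds ratio, with its 95% confidence interval, the primary effect estimate. Centre is not mentioned as a fixed or random effect in {20a} or in {20c}, and no reason is given.

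Protocol article, Background and rationale {6a}: variation in the management of traumatic brain injury is said to go together with unexplained variation in outcome and "large between-center differences unrelated to case-mix".

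Protocol article, Sample size {14}: 300 patients "achieves a 90% power to detect a change in the log odds ratio of 0.69 with a 0.05 (two-sided) significance level", with 8% loss to follow-up and a target odds ratio of 2.0 described in brackets as adjusted.

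**The concern.** Blocking within centre forces the arms to be nearly balanced in every centre. If centres differ in outcome, part of the outcome variation then cannot contribute to the difference between arms. A model without centre does not know this, so its standard error exceeds the true sampling variability of its own estimate and the test is conservative. In a proportional-odds model there is a second effect: leaving out a prognostic factor pulls the common odds ratio towards 1 relative to its within-centre value.

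The article gives reasons to expect centre to matter. The differences reported in {6a} are described as not due to case-mix, and age, GCS and pupillary reactivity are case-mix variables, so they would not absorb them. Sections {11a} and {11d} leave surgical technique, conservative management and concomitant care to each centre. At stake are some power and the interpretation of the main odds ratio.

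**Working it through.** **1. Reproduce the stated sample size.** Inputs from {14} and Table 4: control 25, 10, 10, 10, 10, 15, 20%; surgery 14, 7, 8, 9, 10, 19, 33%; log odds ratio θ = 0.69; power 90%; two-sided α = 0.05; loss 8%. Whitehead's formula for 1:1 allocation is

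N = 12(z₀.₉₇₅ + z₀.₉₀)² / [θ²(1 − Σp̄³)].

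- Mean proportions p̄: 0.195, 0.085, 0.090, 0.095, 0.100, 0.170, 0.265, so Σp̄³ ≈ 0.0341.
- N = 12 × (1.960 + 1.282)² / (0.4761 × 0.9659) ≈ 126.1 / 0.4599 ≈ 274.2, so 275 evaluable.
- 275 / 0.92 ≈ 299, against the stated 300.
- With θ = ln 2 the result is 272 evaluable and 296 in total.
- Power at 300 × 0.92 = 276 evaluable is 90.2% (θ = 0.69) or 90.4% (θ = ln 2).

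The stated figure reproduces from a formula that takes no credit for stratification or covariates.

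**2. Effect of omitting centre.** Simulation with 6,000 trials per setting:

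- 276 evaluable patients, 16 unequal centres, blocks of 2, 4 and 6 within centre.
- Seven-category outcome with Table 4 cut-points and a within-centre odds ratio of 2.0, or 1.0 for type I error.
- One baseline covariate standing in for age, GCS and pupils (assumed log odds ratio 1.0 per SD).
- Normal centre effects with SD σ on the log-odds scale.

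The article gives no σ, so a range is shown. Latent ICC = σ² / (σ² + π²/3): σ = 0.3, 0.5 and 0.8 give 0.027, 0.071 and 0.163. The random-intercept-like fit was given the true variance.

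| ICC | Model | Power, % | Mean OR | Model SE (OR 2.0) | Type I error, % |
|---|---|---|---|---|---|
| 0 | no centre | 89.0 | 2.02 | 0.2222 | 5.5 |
| 0 | random | 89.0 | 2.02 | 0.2222 | 5.5 |
| 0 | fixed | 89.7 | 2.08 | 0.2255 | 6.4 |
| 0.03 | no centre | 88.05 | 1.99 | 0.2219 | 5.0 |
| 0.03 | random | 88.33 | 2.01 | 0.2220 | 5.1 |
| 0.03 | fixed | 89.4 | 2.08 | 0.2260 | 5.8 |
| 0.07 | no centre | 85.95 | 1.95 | 0.2215 | 3.9 |
| 0.07 | random | 87.58 | 2.00 | 0.2223 | 4.4 |
| 0.07 | fixed | 88.8 | 2.07 | 0.2268 | 5.3 |
| 0.16 | no centre | 82.77 | 1.87 | 0.2207 | 3.8 |
| 0.16 | random | 86.80 | 1.99 | 0.2237 | 5.3 |
| 0.16 | fixed | 88.0 | 2.07 | 0.2288 | 6.0 |

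Monte Carlo error is about 0.4 points for power and 0.3 for type I error.

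- Power gain from the random intercept: 0 at ICC 0; 88.33 − 88.05 = 0.28 at 0.03; 87.58 − 85.95 = 1.63 at 0.07; 86.80 − 82.77 = 4.03 at 0.16.
- Adding centre slightly raises the model SE. The gain comes mainly from less attenuation of the odds ratio, together with a less conservative test.
- Why the test is conservative: under the null without centre, the mean model SE is 0.2183 against an actual SD of the estimate of 0.2099 at ICC 0.07, and 0.2179 against 0.2067 at ICC 0.16.

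**3. Does the planned 90% fail?** That depends on what the 2.0 means. A rank-based check used 17 unequal centres, 276 patients, 4,000 trials and centre SD 0.4 / 0.7 / 1.0 (ICC 0.05 / 0.13 / 0.23).

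- If 2.0 is the within-centre odds ratio, the marginal odds ratio is 1.96 / 1.88 / 1.79 and power without centre is 88.1 / 85.0 / 80.6%.
- If Table 4 is the marginal shift and 2.0 the marginal odds ratio, power without centre is 90.7 / 91.1 / 92.3%. Adding centre gains a further 0.6 / 1.8 / 3.0 points.

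**The case against.** The strongest case against acting has four parts.

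- **The loss may be trivial.** Section {6a} gives no variance, and it describes differences that accompany variation in practice. Here the main management decision is randomised within centre, so the remaining centre variance is unknown. This stands, and it limits confidence in the size of the effect.
- **The error is on the safe side.** False positives are not inflated. This also stands.
- **The SAP may add centre.** It is not shown, and such detail often sits there. But {20a} is not silent: it names the covariates behind the primary estimate. If the SAP adds centre, {20a} should be brought into line; if not, the point applies.
- **The random-intercept results are slightly favourable**, because that fit was given the true variance. This stands as a caveat.

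A reader might infer more than the article supports. One inference is that the reported standard error would shrink once centre is added, so that power already paid for is being lost. In fact the model SE rises slightly, and the 300 was never reduced for stratification. Another is that the 90% power is not delivered. That follows only if 2.0 is conditional on centre; the bracketed word in {14} allows that reading, but Table 4 gives arm-level percentages that fit the marginal one. A third is that the covariates themselves are poorly chosen, because patients with "bilaterally absent pupillary responses" are excluded and pre-trauma function appears only as a subgroup. Unilateral abnormality remains eligible, and the article gives no figure for the prognostic strength of either variable, so that is a preference between covariates and not a fault.

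**Conclusion.** The mismatch is in the text: centre is the only stratification factor and is absent from the stated primary model, without a reason. If centres differ at an assumed latent ICC of 0.07 to 0.16, the test is mildly conservative, and a within-centre odds ratio of 2.0 is reported as about 1.95 to 1.87. The power recovered by a random intercept ranges from nothing to about 4 points over ICC 0 to 0.16, and is negligible at 0.03 or below. These sizes rest on assumed centre variance, centre sizes and covariate strength. The analysis as written is valid, if somewhat conservative. This is a free improvement to the primary analysis and does not invalidate the sample size.

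**What to change.** In {20a}, and in the SAP if it differs, specify the primary model as proportional-odds regression of GOS-E at 1 year, categories 1 and 2 combined, on treatment, age, GCS and pupillary reactivity, with a random intercept for centre. Use the same model for GOS-E at the other visits.

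Avoid fixed centre effects. The article gives 17 centres in the Abstract and 8 + 8 = 16 in Study setting {9}; either way there are only about 276 / 17 ≈ 16 to 276 / 16 ≈ 17 evaluable patients per centre. In the simulation, fixed effects pushed the odds ratio to about 2.07 and type I error to 5.3–6.0% when centres differed.

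The cost is one sentence before database lock and no new data. With no true centre variation the random-intercept fit lost no power (89.0% either way). The small downside is that the odds ratio becomes conditional on centre, which the report should state.

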#### Primary study parameter

The average shift over the GOS-E scale caused by early neurosurgical intervention compared to conservative treatment will be calculated using the appropriate tests. The primary analysis set for the primary endpoint is the intention-to-treat (ITT) population. This population must comply with the inclusion criteria and provide informed consent or be included under deferred consent, irrespective of adherence to the allocated treatment.

Our sample size allows us to detect a shift over the GOS-E (see Table 4) from the estimated distribution of conservatively treated patients conform a proportional odds ratio of 2.0 with a power of 90% and a 0.05 significance level (two-sided).

#### Secondary study parameters

For all secondary study parameters, subjects in both arms of the study will be compared using the appropriate tests, based on the ITT population. Graphic data displays may also be used to summarize the data. Statistical analyses may include logistic and linear regression models, Fisher’s exact tests, or chi-square tests and Student’s *t* tests or Mann-Whitney *U* tests (depending on normality of data). The interaction of different operative techniques with treatment arm outcome will be addressed in our subgroup analysis by a Cox Proportional Hazard model with the “day of discharge from the rehabilitation center, nursing, or hospital facility to the own home” as an endpoint/event, which is considered a relevant endpoint from both a QOL and a health-economic perspective. Importantly, analyses of subgroups representing dichotomized continuous variables may also be performed by an interaction-effect analysis.

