
### Objectives {7}

#### Primary objective

The primary objective is to establish the effect of early surgical hematoma evacuation compared to conservative treatment on functional outcome (as expressed by the GOS-E) after 1 year in elderly patients with a traumatic ASDH (Table 1).

**Table 1 Tab1:** The GOS-E score

GOS-E	Category	Description
1	Dead	
2	Vegetative	Condition of unawareness with only reflex responses but with periods of spontaneous eye opening
3	Lower severe disability	Patient fully dependent for all activities of daily living. Requires assistance to be available constantly. Unable to be left alone at night
4	Upper severe disability	Can be left alone at home for up to eight hours but remains dependent. Unable to use public transport or shop by themselves
5	Lower moderate disability	Able to return to work in sheltered workshop or non-competitive job. Rarely participates in social and leisure activities. Ongoing daily psychological problems (quick temper, anxiety, mood swings, depression)
6	Upper moderate disability	Able to return to work but at reduced capacity. Participates in social and leisure activities less than half as often. Weekly psychological problems
7	Lower good recovery	Return to work. Participates in social and leisure activities a little less and has occasional psychological problems
8	Upper good recovery	Full recovery with no current problems relating to the injury

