In this study, the common odds ratio can be interpreted as the average shift over the GOS-E scale at 1 year caused by early neurosurgical intervention compared to non-operative management [90].

The investigators hold the opinion that a potential large shift of patients from GOS-E category 1 (death) to 2 (vegetative state) should not be considered a beneficial effect of surgery and should not result in a positive trial. Therefore, these categories will be combined in the final statistical analysis. As this trial is pragmatic, results will be analyzed according to an intention-to-treat protocol. Predefined subgroups for exploratory analyses are described below. The secondary outcomes will be analyzed using the appropriate tests. A *p*-value of less than 0.05 will be used to indicate statistical significance. For all analyses, commercially available statistical software like SPSS or R will be used.

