#### Cost-effectiveness and cost-utility analysis

An incremental cost-effectiveness ratio (ICER) will be calculated comparing the costs and effects between the surgical and conservative treatment group. A CUA will be performed for which the QALY, calculated based on the EQ-5D-5L summary score, is the outcome measure. For the CEA, the primary effect measure will be the GOS-E. The costs and effects will be discounted. A 1-way, 2-way, and probabilistic sensitivity analysis will be performed to determine the effect of uncertainty in all input parameters.

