### Methods in analysis to handle protocol non-adherence and any statistical methods to handle missing data {20c}

Analyses will be performed on the Full Analysis Set, which is defined by the ICH E9 guidelines “statistical principles for clinical trials” as “The set of subjects that is as close as possible to the ideal implied by the intention-to-treat principle. It is derived from the set of all randomized subjects by minimal and justified elimination of subjects” [94]*.* This means participants will be analyzed according to an intention-to-treat design, which involves analyzing patients according to the treatment arm to which they were initially randomized, including patients receiving delayed neurosurgical intervention after initial randomization to the non-operative arm. If follow-up data from a patient is missing, values will be imputed based on other available follow-up data from that patient. Only patients without any follow-up data (including the 3-month assessment) will be considered “lost to follow-up”. This includes patients whose (deferred) consent is withdrawn before the 3-month follow-up assessment. Patients who have died soon after randomization will be included in the analysis as “death” is one of the outcome categories in the primary outcome measurement (GOS-E). Patients who were wrongfully included due to mistakes in the evaluation of objective entry criteria such as age (eligibility violations) will be considered “non-eligible” in the second instance. The amount of patients “lost to follow-up” or “non-eligible” in the second instance is estimated to be a very small proportion of all study patients (< 5%).

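### The only stated imputation rule treats survivors too brain-injured to complete QOLIBRI, MOCA or EQ-5D-5L like patients who missed a visit, which biases these comparisons and the QALYs

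*Protocol article*

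**What the plan says.** Table 3 schedules QOLIBRI and EQ-5D-5L at 3, 6 and 12 months and then yearly to 5 years, and MOCA at 3, 6 and 12 months. Under Secondary study parameters in {20a}: "For all secondary study parameters, subjects in both arms of the study will be compared using the appropriate tests, based on the ITT population". The tests named there include t tests and Mann-Whitney tests. The EQ-5D-5L also drives the economic result: "A CUA will be performed for which the QALY, calculated based on the EQ-5D-5L summary score, is the outcome measure".

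Items {18b} and {20c} give the same missing-data rule: "If follow-up data from a patient is missing, values will be imputed based on other available follow-up data from that patient". Only a patient with no follow-up data at all counts as lost. Deaths are dealt with through the GOS-E category only.

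Table 1 describes GOS-E 2 as "Condition of unawareness with only reflex responses but with periods of spontaneous eye opening". The section on participants regaining capacity foresees patients who never recover enough to give their own consent. Caregivers are named as a source of answers only for cost items (Cost analysis).

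Item {20a} also sets a principle: "a potential large shift of patients from GOS-E category 1 (death) to 2 (vegetative state) should not be considered a beneficial effect of surgery". It is put into effect by merging GOS-E 1 and 2 in the final analysis.

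**The concern.** An unaware patient cannot fill in a questionnaire or sit a cognitive test, and some fully dependent patients (GOS-E 3) probably cannot do so reliably. These values are missing because the outcome is bad. Filling them from the same patient's other visits goes wrong in two ways:

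- **Testable at some visits only.** A patient in coma at 3 months who later recovers would receive the recovered score for the coma period. A patient who declines would keep the earlier, better score.
- **Testable at no visit.** There is no questionnaire value to draw on. The rule gives no answer, and the standard tests leave the patient out by default.

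Treatment is meant to move patients across exactly these categories, so the affected share should differ between arms. At stake are the QOLIBRI and MOCA comparisons, and a QALY result that could credit the very shift that {20a} says is not a benefit.

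**Working it through.** **Inputs from the protocol (Sample size {14}).** Conservative arm over GOS-E 1-8, in percent: "15, 10, 10, 10, 10, 10, 15, 20) with category 1 and 2 combined". Odds ratio 2.0, 300 patients allocated 1:1, 8% loss, hence 150 × 0.92 = 138 evaluable per arm. The design "achieves a 90% power to detect a change in the log odds ratio of 0.69 with a 0.05 (two-sided) significance level".

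**Check of the plan's own figure.** Whitehead formula with seven categories: N = 12(1.960 + 1.282)² / [0.69² × (1 − Σp̄³)], where p̄ is the mean of the two arms' proportions and Σp̄³ = 0.034. This gives 274.3, so 275, and 275/0.92 rounds up to 299. The stated 300 is reproduced.

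**Size of the affected group.** Dividing the cumulative odds of the eight-category distribution by 2.0 gives the surgery arm 8.1, 6.2, 6.9, 7.8, 8.9, 10.2, 18.5, 33.3%. Merging the first two reproduces the surgery row of Table 4 to within one point.

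| | Conservative | Surgery |
|---|---|---|
| GOS-E 2 | 10.0% (15 of 150) | 6.2% (about 9 of 150) |
| GOS-E 2-3 | 20.0% | 13.1% |
| GOS-E 2-3 among survivors | 20.0/85.0 = 23.5% | 13.1/91.9 = 14.3% |

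**Utility at 1 year, odds ratio 2.0.** The document gives no utilities. Assume 0, 0, 0.1, 0.35, 0.5, 0.65, 0.8, 0.9 for GOS-E 1-8.

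- All scored: conservative 0.010 + 0.035 + 0.050 + 0.065 + 0.120 + 0.180 = 0.460; surgery 0.593; difference 0.133.
- GOS-E 2 omitted: 0.460/0.900 = 0.511 and 0.593/0.938 = 0.632; difference 0.121.
- GOS-E 2-3 omitted: 0.450/0.800 = 0.5625 and 0.586/0.869 = 0.675; difference 0.112.

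A second assumed set has GOS-E 3 at 0.15 and the vegetative state from −0.4 to 0.1. The directly scored difference is then 0.128 to 0.147. It is 0.119 with vegetative patients omitted, and 0.113 to 0.128 when they borrow a value of 0.1 to 0.5 from a better visit. In this scenario surgery's gain is never overstated.

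**Utility at 1 year, pure death-to-vegetative shift.** Surgery moves 8 points from death (15% to 7%) to vegetative state (10% to 18%) and changes nothing else. With both states at 0, the true difference is 0. With vegetative patients omitted and deaths kept at 0: 0.460/0.900 = 0.511 against 0.460/0.820 = 0.561, a false gain of 0.05. At an assumed SD of 0.35 the standard error is 0.35 × √(2/138) = 0.042. For a 10-point shift with a borrowed value of 0.1 to 0.5, the apparent gain is 0.10 × 0.1 to 0.10 × 0.5, that is 0.01 to 0.05. Scored directly with a vegetative utility of −0.4 to 0.1, it is −0.04 to +0.01.

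**QOLIBRI and MOCA, odds ratio 2.0.** Assume scores ordered like the GOS-E, and a tie-corrected Mann-Whitney test in survivors of 138 per arm. With every survivor placed, z = 2.69 and power is 0.77. Omitting GOS-E 2 gives z = 2.32 and power 0.64. Omitting GOS-E 2-3 gives z = 1.94 and power 0.49.

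**Check of a tempting remedy.** Suppose untestable survivors are ranked lowest and deaths excluded. In the 8-point pure shift the probability that a surgery patient scores better is 0.462 and z = −1.04: surgery looks harmful although only deaths became vegetative survival. With both groups unscored, z = 0. Tying deaths and vegetative patients at the bottom also gives z = 0, because the merged share is 25% in both arms.

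**The case against.** A reader might infer that the plan drops vegetative patients and will therefore report a QALY gain from turning deaths into vegetative survival. The text does not support that.

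- A vegetative patient who is visited has GOS-E data and so is not lost to follow-up. For a patient never testable the rule is silent; it does not order exclusion.
- The rule does not prescribe carrying the same questionnaire's score forward or backward. The other follow-up data could include the GOS-E, which is recorded at every visit. Borrowing a better visit's score is the natural reading, not the only one.
- The false gain needs a pure shift, vegetative patients omitted, deaths scored 0 (not stated for QALYs) and assumed utilities. It is about 1.2 standard errors. Under the planned effect the bias runs against surgery.
- Proxy completion is not ruled out, and such detail commonly sits in a full protocol or analysis plan, neither of which is shown. Its absence alone is no finding.
- The principle about death and vegetative state is aimed at the primary result. The economic analysis also counts costs and plans sensitivity analyses on all inputs.
- The power figures concern outcomes for which the trial was not powered. They assume that everyone in the omitted categories is untestable.

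All of this limits the claim. What remains is that the article does state a rule, twice, and that rule makes no exception for inability to answer. A later document that adds a proxy would still have to override it.

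**Conclusion.** The point holds in a limited form. The stated within-patient imputation rule is badly fixed for QOLIBRI, MOCA and EQ-5D-5L, because it treats inability to answer from brain injury as ordinary missingness. In the plan's own figures the group at risk is 10.0% against 6.2% (GOS-E 2), and up to 23.5% against 14.3% of survivors if GOS-E 3 is included.

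The sign of the bias depends on the unknown effect. At odds ratio 2.0, a utility gain of about 0.13 falls to 0.11-0.12. Under a pure death-to-vegetative shift, a gain of up to about 0.05 can appear where the true difference is 0. All utility figures rest on assumed values. The primary GOS-E analysis and the sample size of 300 are unaffected. The change is worth making before the data are seen, because an error of unknown sign cannot be argued away afterwards.

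**What to change.** 1. At each visit, record why a questionnaire is missing, with alive but unable because of brain injury as its own reason. Exempt those values from the within-patient imputation rule in {18b} and {20c}.
2. For EQ-5D-5L and QALYs, take a proxy answer from the caregiver already questioned for costs. Failing that, use a utility by GOS-E category at that visit, fixed before database lock and varied in the planned sensitivity analysis.
3. For QOLIBRI and MOCA, present the comparison in testable survivors as conditional on testability. Add a rank-based sensitivity analysis in which deaths and patients unable because of brain injury are tied at the lowest rank, in line with merging GOS-E 1 and 2. Do not rank untestable survivors lowest with deaths excluded.

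The cost is some wording, one eCRF field, a caregiver EQ-5D-5L at existing contacts and a little more analysis. Proxy and self-rated EQ-5D-5L can differ, which should be acknowledged. No extra patients or visits are needed.
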